### Eligibility criteria {10}

Eligibility criteria for the clusters included not having been previously exposed to the intervention. All women identified as pregnant or within the 6-week postpartum period, presenting for antenatal, intrapartum or postpartum care in the district within the trial time frame will be included. There are no exclusion criteria.

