### Strategies to improve adherence to interventions {11c}

Several strategies have been employed to promote adherence to the intervention protocol. A theory of change workshop bringing together key stakeholders across community, district management and national levels facilitated discussion around the pathways of change for the CRADLE intervention to improve uptake and quality of maternity services, particularly learning from the pilot phase across the first eight districts. Engagement visits to all eight districts were undertaken prior to the feasibility phase and trial. Two offline mobile phone applications were developed to aid primary outcome and process evaluation data collection; both have integrated Global Positioning System (GPS) geotagging capabilities allowing real time monitoring of data collection and CRADLE training adherence. Three-monthly monitoring trips are undertaken to supervise, monitor and audit data collection of primary and secondary outcomes, in addition to real time online data monitoring. Based on the pilot within the first eight districts, the CRADLE training was refined to include a more in-depth focus on emergency obstetric and newborn care (EmONC), increased community engagement to facilitate patient referral acceptance by stakeholders and increased hospital engagement to support adoption of the CRADLE intervention across multi-disciplinary teams and cadres. Full pilot phase implementation strategies will be published elsewhere.

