### Outcomes {12}

Analysis of each outcome will be as a proportion of all deliveries during the six-week period within that district, as assessed from routinely collected data.

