#### Primary outcome measure

The primary outcome is the rate of a composite of maternal mortality, major maternal morbidity and fetal losses (with no double counting) occurring during pregnancy, labour or within 42 days of delivery, including at least one of:Maternal death (all-cause mortality)Eclampsia (occurrence of generalised convulsions with increased blood pressure in the absence of epilepsy or another condition predisposing to convulsions)Emergency hysterectomy (surgical removal of all or part of the uterus)Stillbirth (born without signs of life at or after 28 weeks of gestation)

The primary outcome measures will be assessed by the numbers of events reported at the district (or referral) hospital and the peripheral health units offering the highest level of care (defined as the 20% with the highest level facilities in each district).

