## Data collection and management

### Plans for assessment and collection of outcomes {18a}

Primary outcome data will be collected using a bespoke phone application-based electronic case report form (eCRF). District research officers were provided tablets and data allowance for this purpose. When possible, real-time online data will be uploaded directly into the eCRF, with outcomes therefore recorded directly onto the trial database. The application has been designed to have an offline function given the low availability of internet in many of SL’s rural areas. The outcomes will then upload directly into the study’s electronic database when internet becomes available.

All primary outcomes are robust and meaningful clinical endpoints that are unambiguous and therefore feasible to collect. We have chosen a composite as powering a trial for maternal death alone would require a prohibitively large sample size. We aim to demonstrate the true impact of the intervention across the health system by collecting mortality and morbidity data from hospitals and peripheral health units offering the highest level of care (20% sample. Women presenting to the peripheral health unit and referred to the hospital will be noted, to avoid double counting. Outcomes occurring elsewhere are not included.

The date at first presentation to health facility will be used to determine the period in which a woman experiencing a primary event is analysed in. For example, if a woman presents to the health facility in period one but goes on to be referred to the hospital and suffers an eclamptic fit during period two, she will be analysed within the period one cohort. This is because the district may have received the CRADLE intervention at the beginning of period two; the woman would not have been exposed to the intervention at the time of her initial presentation.

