### Methods for additional analyses (e.g. subgroup analyses) {20b}

We will not be able to collect detailed information (for example breakdown by age or parity) on the total number of deliveries in each district so no subgroup analysis will be possible. No additional analyses based on the per-protocol principle are planned.

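### The primary rate divides events from selected facilities by all recorded deliveries, a post-allocation count the intervention may itself change; the bias is of unknown size and direction

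*Protocol article*

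**What the plan says.** Under Eligibility criteria {10}, pregnant or recently delivered women "presenting for antenatal, intrapartum or postpartum care in the district within the trial time frame will be included". Outcomes {12} expresses every outcome "as a proportion of all deliveries during the six-week period within that district, as assessed from routinely collected data". The count is made afresh in each six-week period, so for a district that has crossed over it is a post-allocation quantity.

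The numerator has a narrower base. Primary outcome measure takes the "numbers of events reported at the district (or referral) hospital and the peripheral health units offering the highest level of care", the latter being the top 20% of units in each district. Plans for assessment and collection of outcomes {18a} adds: "Outcomes occurring elsewhere are not included".

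Strategies to improve adherence {11c} reports a theory-of-change workshop on "the pathways of change for the CRADLE intervention to improve uptake and quality of maternity services". Component 2 has devices handed out in front of community stakeholders to raise awareness.

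Statistical methods {20a} fits linear trends by region and one step at crossover. The only covariates named are the availability of six drugs. Methods for additional analyses {20b} concedes: "We will not be able to collect detailed information (for example breakdown by age or parity) on the total number of deliveries in each district".

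**The concern.** The numerator and the denominator can respond differently to the intervention. A woman who would have delivered unrecorded, and who delivers in a facility after crossover, adds one to the denominator. If she delivers at one of the roughly 80% of peripheral units outside the counted set, any event she has is counted only if she reaches a counted site. A low counted risk among added deliveries is therefore plausible without supposing that these women are unusually healthy.

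A jump in recorded deliveries at crossover coincides with the model's treatment step and would be absorbed by it. The rate could then fall while the number of deaths, stillbirths, eclampsia cases and hysterectomies stays the same. With no age or parity breakdown of deliveries, a change in case mix can be neither seen nor adjusted for.

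**Working it through.** **Inputs from the protocol article.** Sample size estimation {14}: 5% falling to 4%, eight districts, about 1000 deliveries per district-period, CAC 1. Figure 3 caption: ICC 0.01, 0.02 and 0.5. Sequence generation {16a}: Falaba and Bonthe are paired, so there may be seven sequences and eight periods rather than eight and nine. Statistical methods {20a}: significance at 0.05, taken as two-sided.

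**Assumptions, not in the document.** x is the proportional rise in recorded deliveries at crossover. r is the counted risk of the added deliveries relative to the usual 5%. The true effect is nil.

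**The plan's own figure first.** I used a generalised least squares variance for cluster-period means with categorical period effects and a normal approximation. At ICC 0.5, CAC 1 and a mean risk of 4.5%, power for 5% against 4% is 99.9% with eight sequences and 99.8% with seven. The stated power of close to 100% is reproduced. At ICC 0.01 and CAC 1 it is 96% and 94%.

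**Dilution.** Before crossover there are N deliveries and 0.05N events. Afterwards there are N(1 + x) deliveries and 0.05N(1 + rx) events. So

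apparent RR = (1 + rx) / (1 + x).

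At x = 10%:
- r = 0: 1/1.10 = 0.909
- r = 0.25: 1.025/1.10 = 0.932
- r = 0.5: 1.05/1.10 = 0.955
- r = 1: 1.10/1.10 = 1.00

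The spurious shift is d = 5 × (1 − RR) percentage points, against a 1.0-point target.

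**Chance of a significant result.** P = Φ(d/SE − 1.96) + Φ(−d/SE − 1.96), at ICC 0.01, CAC 1 and 1000 per cell:

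| r | RR | d (points) | 8 sequences, p = 0.045 (SE 0.269) | 8 sequences, p = 0.05 (SE 0.283) | 7 sequences, p = 0.05 (SE 0.301) |
|---|---|---|---|---|---|
| 0 | 0.91 | 0.45 | 39.4% | 36.3% | 32.7% |
| 0.25 | 0.93 | 0.34 | 24.5% | 22.6% | 20.5% |
| 0.5 | 0.95 | 0.23 | 13.5% | 12.7% | 11.7% |
| 1 | 1.00 | 0 | 5% | 5% | 5% |

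The seven-sequence column puts the pair at the first step; a middle step changes each figure by less than one percentage point. With CAC 0.9, eight sequences and p = 0.05, the r = 0 figure falls to about 21%. The planned permutation test with regional linear trends is not this model, so these are orders of magnitude.

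**Rise needed to mimic the full target.** Setting RR = 0.80 gives x = 0.20/(0.80 − r): 25% at r = 0, 36% at r = 0.25 and 67% at r = 0.5.

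**The opposite direction.** If better referral raised the share of events reaching counted sites from 80% to 88% (assumed) with deliveries unchanged, RR = 0.88/0.80 = 1.10. With a 10% rise in deliveries at r = 0.2 as well, RR = (1.10 + 0.02)/1.10 = 1.02.

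**A denominator that does not respond.** RR = 1 + rx, which at x = 10% is 1.00, 1.025 and 1.05 for r = 0, 0.25 and 0.5. With no true effect, the two analyses therefore lie on either side of 1, or at it.

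**The case against.** The strongest objection is that the text does not establish a rise in facility deliveries. Outcomes {12} speaks of all deliveries in the district; if routine data captured home births too, the denominator would not respond to uptake. The document does not say that they do. The support for higher uptake is one general phrase from a workshop. The stated purpose of community engagement in {11c} is acceptance of referral, and the awareness aim in Component 2 concerns antenatal care. This stands: the rise is a possibility, not a documented expectation.

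A reader might infer that the eligibility rule admits women only after crossover, and so builds in identification bias favouring the intervention. The document does not support that. Eligibility runs over the whole trial time frame, and antenatal attendance already brings in a woman who delivers at home. An event's period is set elsewhere: "The date at first presentation to health facility will be used to determine the period". Nor is the direction fixed, since referral to higher-level sites is an explicit aim and would raise counted events.

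It can also be said that sensitivity analyses belong in an analysis plan that is not shown. Their absence here is indeed no fault. The denominator, the counted facilities and the lack of case-mix data are, however, fixed in the article itself. The process evaluation does examine reach and referrals and relates process measures to the primary outcome, but it does not name delivery counts.

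**Conclusion.** The point holds as a vulnerability of the primary rate, not as a demonstrated bias. For an assumed 10% rise in recorded deliveries and no true effect, the apparent risk ratio lies between 0.91 and 0.95 when added deliveries carry between none and half of the usual counted risk. It would be declared significant in roughly 12% to 39% of trials, depending on that risk, the baseline proportion and the number of sequences. These figures rest on ICC 0.01, CAC 1 and 1000 deliveries per cell, and on values of x and r that the document does not give. At equal risk the bias is nil, and improved capture of events could reverse it.

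It would go too far to say that the whole 20% target could readily be an artefact: that needs a rise of at least 25%, even if every added delivery is event-free. Because size and net direction are unknown, the denominator should be examined rather than presumed stable.

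**What to change.** In Outcomes {12} and Statistical methods {20a}, add two items.

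1. Analyse recorded deliveries per district-period as an outcome in the same stepped-wedge framework, to show whether the denominator steps at crossover.
2. Add a supportive sensitivity analysis of composite event counts over a denominator that does not respond to the intervention: expected births from district population, or pre-trial delivery counts if they exist. The feasibility-phase section mentions only primary outcome data, so those counts should not be taken for granted. Report the result beside the primary rate, so that the two bracket the effect.

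State that if deliveries step at crossover, or the two analyses diverge, a fall in the rate cannot be attributed to fewer events alone. Agreement should not be a condition for interpreting the primary result: better event capture could make the supportive analysis look worse and so wrongly cancel a real benefit.

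The cost is mainly analysis wording, since delivery counts per period are already needed for the primary rate. The drawbacks are that a fixed denominator misses district-specific changes in births and that its numerator is still affected by improved capture of events.

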### Who will take informed consent? {26a}

In accordance with recognised procedures for stepped-wedge cluster trials [18], institutional-level consent and relevant local approvals from district health authorities and hospitals on behalf of the cluster will be obtained at the start of the trial (time point zero), prior to implementation of the intervention at subsequent time points.

### Additional consent provisions for collection and use of participant data and biological specimens {26b}

Written informed consent will be sought from women, healthcare providers and community members participating in qualitative interviews and focus group discussions undertaken as part of the process or scale-up evaluation. A gatekeeper (for example a community chief) will facilitate the team to approach potential participants and a research assistant will discuss the study, give an information sheet and respond to any queries or concerns of those interested in taking part. Up to 24 h will be given to consider participation. The participant information materials and informed consent form to participate in qualitative interviews and focus group discussions are available from the corresponding author on request.

## Interventions

### Explanation for the choice of comparators {6b}

Prior to transitioning to the CRADLE intervention, all women will be managed according to local guidelines (see https://mohs2017.files.wordpress.com/2018/04/sl-emonc-protocols-and-guidelines-a4-final.pdf to access national guidelines for emergency obstetric and newborn care). None of the districts will receive the intervention at time point 0. One district will be randomly allocated to receive the intervention at time point 1, whilst all the remaining areas contribute to the control at this time point. A second district is randomly allocated to the intervention at time point 2 and so on. Each randomisation cluster will cross over from the control to the CRADLE intervention at six-weekly intervals (see Fig. 2).

**Fig. 2 Fig2:**
[figure not shown]
Standard Protocol Items: Recommendations for Intervention Trials (SPIRIT) figure

At the time each district is randomised to receive the CRADLE intervention, all levels of healthcare providers within that district, involved in the care of pregnant and postpartum women, will get access to the CRADLE VSA device and will be trained using the train-the-trainer model.

### Intervention description {11a}

The CRADLE intervention consists of two components and is described according to the TIDieR checklist [22].

#### Component 1—Microlife® CRADLE Vital Sign Alert device

The Microlife® CRADLE VSA is a hand-held, upper-arm, semi-automated device that measures BP and pulse. The device has undergone extensive testing for accuracy and is one of few BP devices to have been validated as accurate in pregnancy (including pre-eclampsia and hypotension) and in non-pregnant adults [11, 23, 24]. It is cost-effective (less than $20) and can be used effectively by unskilled personnel after minimal training. The device incorporates a traffic-light early warning system that alerts all levels of healthcare provider to abnormalities in vital signs, secondary to obstetric haemorrhage, sepsis and hypertension [23, 25, 26]. The thresholds that trigger the traffic lights were determined through pregnancy-specific prediction studies. The device fulfils the World Health Organization requirements for low-resource settings [24]. Other unique developments suited to low-income countries include a micro-USB charging ability and a “traffic light” early warning system for hypertension and shock (secondary to either obstetric haemorrhage or sepsis). The CRADLE intervention will be incorporated into routine maternity care. All primary and secondary level health facilities in eight districts will be provided with CRADLE VSA devices and emergency obstetric triage training via the Train-the-Trainer model. Devices are allocated per health facility according to health facility size and capacity, with 30% total stock kept at the district stores as buffer stock.

#### Component 2—CRADLE Training programme

A face-to-face training programme will be rolled out to a selected sample of locally selected CRADLE champions, district stakeholders and key maternal health partners in the district headquarter towns by the central CRADLE team, comprising two senior midwives and the program manager. The training package is as described below but can be adapted to meet specific contextual factors. It includes a short, animated video describing the device and how it is used (https://cribs-i.org/professionals/cradle-vsa/microlife-cradle-vsa-user-guide/), an interactive session with the trainees, a reference booklet, a wall poster showing how the device is used and an aide-memoire card attached to the CRADLE device for quick reference. The animated film is in English and has also been translated into Krio, the most commonly spoken language across Sierra Leone. The content of this training material covers: (1) use of the Microlife CRADLE VSA device, (2) basic clinical assessment of pregnant women, (3) understanding pre-eclampsia, eclampsia, obstetric haemorrhage and sepsis and review of local management guidelines and protocols, (4) triggers for treatment and/or referral and familiarisation with local referral pathway, (5) CRADLE VSA device troubleshooting and (6) CRADLE VSA maintenance manual.

Components of the training have been adapted to meet the SL specific contextual needs: the training was expanded to include a more extensive focus on Emergency Obstetric and Newborn Care (EmONC) training as well as an increased focus on community engagement, training facilitation tips, respectful maternity care and a CRADLE maintenance practical session. A training aide in the form of the CRADLE song, to a local popular tune, was integrated.

Champions were encouraged to follow the ten-step training content approach:Explain CRADLE (CRADLE video)Explain the traffic lightsExplain the arrowsExplain the different scenarios and their managementPractical demonstration of how to use the deviceExplain respectful maternity care and role play to communicate CRADLE results with womenDemonstrate how to document the CRADLE resultsPractical session using the CRADLE observation checklistExplain how to maintain CRADLE and explain the “Replace & Repair” systemSing the CRADLE Song

Following training, the CRADLE champions return to their allocated local community health centres (three or four maximum) and deliver the devices and associated training. Additional CRADLE Champions are selected from the district hospitals to target the higher numbers of staff working within hospital settings. CRADLE Champions are encouraged to conduct the device distribution with involvement and in the presence of key community stakeholders, to raise awareness of the CRADLE intervention and its impact on supporting maternal health and antenatal care delivery at community level.

### Criteria for discontinuing or modifying allocated interventions {11b}

There are no criteria for discontinuing the intervention given it is a validated, accurate device and vital signs measurement is part of standard care during pregnancy and the post-partum period. The CRADLE devices and training materials will continue to be available across the healthcare system at the end of the trial.

### Strategies to improve adherence to interventions {11c}

Several strategies have been employed to promote adherence to the intervention protocol. A theory of change workshop bringing together key stakeholders across community, district management and national levels facilitated discussion around the pathways of change for the CRADLE intervention to improve uptake and quality of maternity services, particularly learning from the pilot phase across the first eight districts. Engagement visits to all eight districts were undertaken prior to the feasibility phase and trial. Two offline mobile phone applications were developed to aid primary outcome and process evaluation data collection; both have integrated Global Positioning System (GPS) geotagging capabilities allowing real time monitoring of data collection and CRADLE training adherence. Three-monthly monitoring trips are undertaken to supervise, monitor and audit data collection of primary and secondary outcomes, in addition to real time online data monitoring. Based on the pilot within the first eight districts, the CRADLE training was refined to include a more in-depth focus on emergency obstetric and newborn care (EmONC), increased community engagement to facilitate patient referral acceptance by stakeholders and increased hospital engagement to support adoption of the CRADLE intervention across multi-disciplinary teams and cadres. Full pilot phase implementation strategies will be published elsewhere.

### Relevant concomitant care permitted or prohibited during the trial {11d}

No routine concomitant care will be withheld during the trial.

### Provisions for post-trial care {30}

As sponsor, King’s College London has specialist insurance policy in place which would operate in the event of any participant suffering harm because of their involvement in the research. However, the CRADLE intervention (i.e. blood pressure and pulse measurement, and training) is an international standard, is of minimal risk and does not adversely affect the rights and welfare of the individual women.

### Outcomes {12}

Analysis of each outcome will be as a proportion of all deliveries during the six-week period within that district, as assessed from routinely collected data.

